## **15. Analysis plan:**

1. Test if the lower bound of the 95% CI of the GI Genius CADx optical diagnosis NPV for diminutive ( $\leq 5$  mm) rectosigmoid polyps is greater or equal than 90%.
2. Test if agreement in assignment of post-polypectomy surveillance intervals of the enrolled patients according to PIVI guidelines between:
  - a. the combined use of GI Genius CADx as optical diagnosis for diminutive ( $\leq 5$  mm) polyps and conventional histology as diagnostic tool for polyps  $> 5$  mm, and
  - b. histology as diagnostic tool for all the resected polyps (regardless of size).has a lower bound of the 95% CI greater or equal than 90%.
3. Report descriptive analysis of Sensitivity, Specificity, Accuracy, PPV and NPV of GI Genius CADx optical diagnosis
4. Report descriptive analysis of Sensitivity, Specificity, Accuracy, PPV and NPV of the optical diagnosis of endoscopists assessing lesions in white-light with the help of GI Genius CADx
5. Report descriptive analysis of Sensitivity, Specificity, Accuracy, PPV and NPV of the optical diagnosis of endoscopists assessing lesions with virtual chromoendoscopy and without the help of GI Genius CADx

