| 9. Inclusion/Exclusion criteria:

Inclusion criteria: 
 
Patients aged 40 years or older undergoing screening colonoscopy for CRC
 
Ability to provide written, informed consent (approved by EC) and understand the responsibilities of trial participation.
 
 Exclusion criteria: 
 
subject at high risk for CRC;
 
subjects with a personal history of CRC, IBD or hereditary polyposis or non-polyposis syndromes;
 
patients with previous resection of the sigmoid rectum;
 
patients on anticoagulant therapy, which precludes resection / removal operations due to histopathological findings;
 
patients who perform an emergency colonoscopy.
 
                                                                                                                                                                                                                                                                                                                                                                                                                                                                                                                                                                                                                                                                                                                                                                                                                                                                                                                                                                                                                                                                                                                                                                                                                                                                                                                                                                                                                                                                                                                                                                                                                                            |

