### **Exploratory endpoints:**

1. Agreement in assignment of post-polypectomy surveillance intervals according to PIVI guidelines between:
  - the assignment identified according to the combined GI Genius CADx optical diagnosis for diminutive ( $\leq 5$  mm) polyps and histology for larger polyps ( $> 5$  mm), and
  - the assignment identified according to histology alone regardless of lesion size.
2. Sensitivity, Specificity, Accuracy, PPV and NPV of GI Genius CADx optical diagnosis
3. Sensitivity, Specificity, Accuracy, PPV and NPV of the optical diagnosis of endoscopists assessing lesions in white-light with the help of GI Genius CADx
4. Sensitivity, Specificity, Accuracy, PPV and NPV of the optical diagnosis of endoscopists assessing lesions with virtual chromoendoscopy and without the help of GI Genius CADx

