## 2. STUDY RATIONALE AND DESIGN

### 2.1 Study objective

Primary object of the study is to prospectively evaluate if GI Genius CADx output can achieve  $\geq 90\%$  Negative Predictive Value in characterization (i.e. as adenomas or non-adenomas) of diminutive rectosigmoid polyps (i.e. PIVI 2), having conventional histopathology analysis of the resected specimens as reference standard. An exploratory objective of the study is to assess if there is an agreement between the post-polypectomy

surveillance intervals assigned by a combined use of GI Genius CADx as a means for optical diagnosis of diminutive ( $\leq 5$  mm) rectosigmoid polyps and conventional histology of polyps  $> 5$  mm, and those assigned by histology as unique means of diagnosis of all polyps (regardless of size or location).

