### 10.2 Exploratory endpoints:

1. Agreement in assignment of post-polypectomy surveillance intervals of the enrolled patients according to established guidelines between:
  - the combined use of GI Genius CADx as optical diagnosis for diminutive ( $\leq 5$  mm) polyps and conventional histology as diagnostic tool for polyps  $> 5$  mm,
  - and*
  - histology as diagnostic tool for all the resected polyps (regardless of size or location).

2. Sensitivity, Specificity, Accuracy, PPV and NPV of GI Genius CADx optical diagnosis.
3. Sensitivity, Specificity, Accuracy, PPV and NPV of the optical diagnosis of endoscopists assessing lesions in white-light with the help of GI Genius CADx.
4. Sensitivity, Specificity, Accuracy, PPV and NPV of the optical diagnosis of endoscopists assessing lesions with virtual chromoendoscopy and without the help of GI Genius CADx.

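### The exploratory surveillance-interval agreement test is defined on two different polyp sets, and its all-enrolled denominator can include patients who agree by construction

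*Protocol*

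**What the plan says.** All references are to the CHANGE part of the protocol unless stated.

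- **Objective** (synopsis section 6 and section 2.1). The exploratory objective combines optical diagnosis of diminutive "rectosigmoid polyps and conventional histology of polyps" larger than 5 mm. It compares this with histology of every polyp, whatever its size or location.
- **Endpoint** (synopsis section 14, exploratory item 1). The combined arm is "the assignment identified according to the combined GI Genius CADx optical diagnosis for diminutive" polyps, with no location limit. No patient population is named.
- **Endpoint** (section 10.2, item 1). The measure is "Agreement in assignment of post-polypectomy surveillance intervals of the enrolled patients according to established guidelines between" two strategies, the first being "the combined use of GI Genius CADx as optical diagnosis for diminutive" polyps plus histology for larger ones. Again there is no location limit.
- **Analysis** (synopsis section 15, item 2). "Test if agreement in assignment of post-polypectomy surveillance intervals of the enrolled patients according to PIVI guidelines between" the same two strategies, without a location limit. The success rule is that agreement "has a lower bound of the 95% CI greater or equal than 90" per cent.
- **Performance standard** (synopsis section 5 and section 1.1, first standard). The 90% agreement benchmark is described for polyps up to 5 mm without a location limit.
- **Eligibility** (synopsis section 9). The entry criterion is "Patients aged 40 years or older undergoing screening colonoscopy for CRC", plus consent. No polyp is required.
- **Guideline.** Synopsis sections 14 and 15 name PIVI as the basis for the intervals. Section 10.2 refers only to established guidelines.

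**The concern.** There are two separate problems.

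First, the objective and the test describe different combined strategies. Under the objective, a diminutive polyp in, say, the ascending colon gets neither optical diagnosis nor histology in the combined arm, yet it counts in the comparator. Under the endpoint and the analysis it gets optical diagnosis. The same patient could be assigned different intervals under the two definitions, so a formal pass/fail rule is attached to an outcome that the protocol does not fix. The two wordings for the surveillance guideline leave the rule that generates the intervals open as well.

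Second, the two strategies differ only in how diminutive polyps are read. A patient without one gets the same interval from both. If such patients are in the denominator, each adds a certain agreement, which raises both the observed proportion and its lower bound. A pass could then partly reflect case mix rather than optical diagnosis.

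**Working it through.** **Polyp set.** No arithmetic is needed.

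| Place | Optical diagnosis applies to | Histology applies to | Diminutive polyp outside the rectosigmoid |
|---|---|---|---|
| Objective (synopsis 6; 2.1) | diminutive rectosigmoid | >5 mm | no method |
| Endpoint (synopsis 14; 10.2) | all diminutive | >5 mm | optical diagnosis |
| Analysis (synopsis 15) | all diminutive | >5 mm | optical diagnosis |

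The rows cannot all hold.

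**Denominator: inputs.**
- Enrolment of at least 156 (synopsis section 16: 148 × 1.05 = 155.4, rounded up to 156). This size is for the NPV endpoint. The protocol gives no power or expected value for agreement, so there is no figure of its own to reproduce here.
- Success rule: lower 95% bound ≥ 90%. The interval method is not stated; I use Clopper-Pearson. Wilson gives the same cut-off at 156.
- Share f of included patients without a diminutive polyp: not in the documents, so assumed over a range.

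**Step 1: cut-off at 156.** With 8 disagreements, 148/156 = 94.9% and the lower bound is 90.1%: pass. With 9, 147/156 = 94.2% and the lower bound is 89.3%: fail. So at most 8 disagreements are allowed. (The 148 agreements are 156 − 8 and are unrelated to the 148 subjects in the sample-size section.)

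**Step 2: effect of f.** Patients who can disagree: k = 156(1 − f), rounded. With true agreement of 90% among them, the chance of passing is P(X ≤ 8), X ~ Binomial(k, 0.10). The observed agreement needed among them is (k − 8)/k. The true agreement among them that corresponds to 90% overall is (0.90 − f)/(1 − f). The last column restricts the test to the k patients and uses the exact cut-off for that k.

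| f (assumed) | k | Observed agreement needed | True agreement equal to 90% overall | Chance of passing, all enrolled | Restricted test: disagreements allowed; chance of passing |
|---|---|---|---|---|---|
| 0 | 156 | 94.9% | 90.0% | 2.2% | 8; 2.2% |
| 4% | 150 | 94.7% | 89.6% | 3.1% | 7; 1.4% |
| 10% | 140 | 94.3% | 88.9% | 5.3% | 6; 1.1% |
| 20% | 125 | 93.6% | 87.5% | 11.2% | 5; 1.1% |
| 30% | 109 | 92.7% | 85.7% | 22.7% | 4; 1.3% |

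The 95% bound implies a one-sided error of 2.5%. The restricted test stays below it; the all-enrolled rule exceeds it from f = 4% upwards in this table.

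**Step 3: what the protocol's lesion yield suggests about f.** The Standalone CADx synopsis (study procedure) expects 500 to 800 lesions in 156 participants: 500/156 = 3.2 and 800/156 = 5.1 per patient. If counts were Poisson, the share with no polyp would be exp(−3.2) = 4% down to exp(−5.1) = 0.6%. If counts were overdispersed (negative binomial with k = 1, an assumption), it would be 1/(1 + 3.2) = 24% down to 1/(1 + 5.1) = 16%. Patients with only larger polyps add an unknown amount. Under the objective's rectosigmoid wording, patients whose diminutive polyps all lie elsewhere could be added too.

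**The case against.** The strongest reply concerns the denominator. The endpoint is a post-polypectomy interval, and a patient with no polypectomy has none to compare. The reference to enrolled patients may only name the patient, rather than the polyp, as the unit, and the exact analysis set may be left to the statistical analysis plan. The quoted performance standard is itself a whole-strategy measure that does not restrict patients, so an all-patient estimate is a legitimate quantity. Most of this stands. It removes any certainty that patients without polyps count as agreements. It does not remove patients whose polyps are all above 5 mm, who do have a post-polypectomy interval and still cannot disagree.

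A reader might infer that the test is heavily diluted: with one third of patients uninformative and true agreement of 85% in the rest, overall agreement would be 1/3 + 2/3 × 0.85 = 90%. The documents do not support that. They give no uninformative share, they call diminutive polyps the majority of those detected, and their expected yield is compatible with a share of a few per cent.

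On the polyp set, it can be said that the endpoint, the analysis and the standard agree, so the operative test is clear and the objective carries a stray word. That lowers the severity, but the objective still contradicts the test and leaves some polyps without a method.

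**Conclusion.** The inconsistency in the polyp set is certain and rests on the text alone: the objective and the test define different combined strategies. The denominator point holds in a limited form. To the extent that patients without a diminutive polyp are included, they agree by construction, and the effect runs only towards passing. Its size is not fixed by the documents. At 156 patients and true agreement of 90% among those who can disagree, the chance of passing runs from 2.2% with none uninformative to 22.7% at an assumed 30%, and 3.1% at 4% is compatible with the protocol's own lesion yield. These figures assume exact binomial limits, independent patients and full enrolment of 156.

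Severity is minor. The endpoint is labelled exploratory and the sample size is tied to NPV only. A reader might infer that the primary NPV conclusion is affected; nothing in the protocol links it to this test.

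**What to change.** 1. In synopsis section 6 and section 2.1, delete the word rectosigmoid from the agreement objective, so that it uses the same polyp set as synopsis sections 14 and 15 and section 10.2. The NPV objective keeps its rectosigmoid restriction.
2. In synopsis section 15, item 2, and section 10.2, item 1, base the test on patients with at least one resected diminutive polyp, whether or not CADx gave a prediction. Requiring a CADx diagnosis would select on device output, because patients whose diminutive polyps all returned no prediction would drop out. Report the all-enrolled figure as supportive.
3. Use the same surveillance guideline wording in synopsis sections 14 and 15 and section 10.2.

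The cost is wording plus one changed denominator. Polyp size and location, CADx output and histology are already recorded in the CRF, so no new data are needed. The denominator becomes somewhat smaller, the interval wider and the agreement figure less favourable.

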**16. Sample size:**

A previous pilot study involving GI Genius CADx on 40 patients, reported an optical diagnosis of “non-adenoma” on 22 out of 23 assessed recto-sigmoid hyperplastic diminutive polyps, and could not reach an optical diagnosis on 1 polyp. The sample size calculation is therefore conservatively assuming that GI Genius CADx has an NPV between 95.6% (worst case analysis) and 100% on diminutive recto-sigmoid polyps and will therefore consider 97.8% as the expected NPV performance.

Using a one-sided alpha level of 0.025, a total of 148 subjects is required to achieve 80% power to meet the primary endpoint of the study, which is increased by 5% to account for drop-out rate. The number of subject to be enrolled will therefore be at least 156 patients.

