## **14. Study endpoints:**

### **Primary endpoint:**

- Negative Predictive Value (NPV) of GI Genius CADx optical diagnosis on diminutive ( $\leq 5$  mm) rectosigmoid polyps.

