## 2.5 Sample size

A previous pilot study involving GI Genius CADx in 40 patients, reported an optical diagnosis of “non-adenoma” on 22 out of 23 assessed recto-sigmoid hyperplastic diminutive polyps, and could not reach an optical diagnosis on 1 polyp. The sample size calculation is therefore conservatively assuming that GI Genius CADx has an NPV between 95.6% (worst case analysis) and 100% on diminutive recto-sigmoid polyps and will therefore consider 97.8% as the expected NPV performance.

Using a one-sided alpha level of 0.025, a total of 148 subjects is required to achieve 80% power to meet the primary endpoint of the study. Anticipating a 5% drop-out rate, the target is to enroll at least 156 patients.

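### The CHANGE sample size takes a pilot specificity (22 of 23 hyperplastic polyps called non-adenoma) for an NPV, so the 80% power stated for the primary NPV test is unsupported

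*Protocol*

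**What the plan says.** In the CHANGE protocol the primary endpoint (synopsis item 14, repeated in section 10.1) is the "Negative Predictive Value (NPV) of GI Genius CADx optical diagnosis on diminutive" rectosigmoid polyps. Synopsis item 15 sets the test: success if the lower bound of the 95% CI for NPV on diminutive "rectosigmoid polyps is greater or equal than 90"%.

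Synopsis item 16, repeated in section 2.5, gives the planning basis. It starts with "A previous pilot study involving GI Genius CADx on 40 patients", in which the device gave a non-adenoma diagnosis "on 22 out of 23 assessed recto-sigmoid hyperplastic diminutive polyps, and could not reach an optical diagnosis on 1 polyp". From this it proceeds by "conservatively assuming that GI Genius CADx has an NPV between 95.6% (worst case analysis) and 100% on diminutive recto-sigmoid polyps", and takes 97.8% as the expected value. It continues: "Using a one-sided alpha level of 0.025, a total of 148 subjects is required to achieve 80% power". A 5% dropout allowance brings enrolment to at least 156 patients.

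**The concern.** NPV is the proportion of polyps called non-adenoma that really are non-adenoma. Its denominator is set by the device's call. The pilot proportion has the opposite conditioning: its denominator is polyps with hyperplastic histology, and it counts how many the device called non-adenoma. That is specificity, here with a no-call counted as a failure.

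Only adenomas called non-adenoma lower an NPV below 100%. Neither item 16 nor section 2.5 says how many pilot adenomas there were or how the device called them. The planning NPV therefore carries no information on the one error that decides the primary test.

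The lower end of the range shows the confusion. The polyp that turns 22/22 into 22/23 was hyperplastic and received no diagnosis. It is not a non-adenoma call, so it lies outside the NPV denominator, and because it is not an adenoma it could not have been a false negative either.

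Finally, the plan describes its assumption as conservative but uses the middle of its own range, not the lower end.

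At stake is the justification for the enrolment target and the power claim of the primary endpoint. If the true NPV is above 90% but below 97.8%, a failed primary test could be the likely result for a device that does exceed the threshold, and the protocol would give no warning of it.

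**Working it through.** **Inputs from the CHANGE protocol.** Threshold p0 = 0.90 (item 15). One-sided alpha 0.025, power 80%, 148 subjects, 5% dropout, expected NPV 97.8%, pilot 22/23 in 40 patients (item 16 and section 2.5).

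**1. Where 97.8% comes from.** 22/23 = 0.9565 and 22/22 = 1. The midpoint is (0.9565 + 1)/2 = 0.978. Both ends use hyperplastic polyps only.

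**2. Reproducing 148.** For a one-sample binomial test of 0.90 against 0.978:

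- Normal (score) formula: n = [(1.960·√(0.90·0.10) + 0.842·√(0.978·0.022)) / 0.078]² = 83.2, so 84 polyps.
- Exact binomial: 85 is the smallest n from which power stays at or above 80%.
- Pilot yield: 23/40 = 0.575 polyps per patient. 85/0.575 = 147.8, so 148 patients.
- Dropout: 148 × 1.05 = 155.4 and 148/0.95 = 155.8; both round up to 156.

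The plan's figure is recovered. The document does not print the 85 or the 0.575; this is a reconstruction. The yield again counts histologically hyperplastic polyps, not non-adenoma calls.

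**3. What specificity 22/23 implies for NPV.** With prevalence π of adenoma,

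NPV = spec·(1 − π) / [spec·(1 − π) + (1 − sens)·π].

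Sensitivity and prevalence are not in the document. The values below are assumptions.

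| Adenoma prevalence | NPV at sens 80% | NPV at sens 90% | NPV at sens 95% | Sensitivity needed for NPV 97.8% |
|---|---|---|---|---|
| 20% | 95.0% | 97.5% | 98.7% | 91% |
| 30% | 91.8% | 95.7% | 97.8% | 95% |
| 40% | 87.8% | 93.5% | 96.6% | 97% |
| 50% | 82.7% | 90.5% | 95.0% | 98% |

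The same specificity is compatible with NPVs from about 83% to 99%.

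**4. How power depends on the true NPV.** Success means a lower exact (Clopper-Pearson) 95% bound of at least 0.90. Polyps are taken as independent. With 85 non-adenoma calls this needs at least 82 correct (lower bound 0.9003); with 148 it needs at least 141. Power is the binomial probability of reaching that count.

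| True NPV | 85 non-adenoma calls | 148 non-adenoma calls |
|---|---|---|
| 97.8% | 88% | 98% |
| 95.65% | 49% | 68% |
| 94% | 24% | 33% |
| 93% | 15% | 18% |

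The exact figures move in steps with n: at 95.65% power is 29% for n = 84, 49% for 85, 45% for 90 and 56% for 100. The score approximation at n = 85 gives 81% at 97.8% and 37% at 95.65%.

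**The case against.** Several objections have force.

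- **The calculation itself is sound.** Given 97.8%, 148 subjects follows. This stands: the fault is in the planning input, not in the arithmetic.
- **The validity of the result is not touched.** The confidence-interval rule in item 15 does not use the planning value, so type I error and the meaning of a positive result are unaffected. This stands; only the power justification is at issue.
- **The number of usable polyps may be well above 85.** The Standalone CADx protocol expects about 500 to 800 lesions from the 156 patients, and the CHANGE background says most detected polyps are diminutive, especially in the rectosigmoid. About 185 non-adenoma calls would give roughly 80% power even at 95.6%; that is 23% to 37% of the forecast (185/800 and 185/500). The share that will be diminutive, rectosigmoid and called non-adenoma is not given, so this can be neither claimed nor excluded.
- **The pilot may have had no false negatives.** A high NPV could then be defended. The text does not say so.
- **Stating enrolment in subjects is normal.** Agreed. The unit is not wrong; the conversion behind it is simply not shown.

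A reader might also infer that the true power is 49%. The documents do not support that. It would enter 95.65% as an NPV when that figure is not one, and it rests on 85 calls and an exact interval, neither of which the protocol states.

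**Conclusion.** The point holds for the planning input. The expected NPV of 97.8%, and with it the stated 80% power for the primary endpoint, rests on a specificity, and nothing else in the document supplies an NPV. Describing the midpoint as conservative is also incorrect.

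The size of the effect can only be shown as a range. Over NPVs of 93% to 97.8%, power runs from 15% to 88% with 85 non-adenoma calls and from 18% to 98% with 148. These figures assume independent polyps, so clustering within patients is ignored, and an exact 95% CI.

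It would go too far to conclude that the trial is underpowered, or that enrolment is too small or already sufficient. The actual power depends on an NPV and a number of non-adenoma calls that the document does not give.

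**What to change.** In CHANGE synopsis item 16 and section 2.5:

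1. Call 22/23 a specificity, with the no-call counted as a failure. Delete the word *conservatively* and the midpoint argument.
2. Derive the expected NPV from all pilot non-adenoma calls, split into true and false, or from stated values of sensitivity, specificity and adenoma prevalence in diminutive rectosigmoid polyps.
3. Show the assumed number of diminutive rectosigmoid polyps called non-adenoma per patient that turns the polyp requirement into 148 subjects.
4. Replace the flat 80% with power at 156 patients over a range of NPV (for example 93% to 97.8%) and of evaluable polyps.

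Keep the confidence-interval rule in item 15 as the decision rule. It applies to whatever number of non-adenoma calls occurs, so no fixed limit on false negatives is needed.

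The cost is two reworded paragraphs and a re-tabulation of pilot data. The stated power will look less favourable. Whether enrolment needs to change can be judged only once the corrected NPV and yield are in place.
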